## Discussion

The study protocol of the proposed trial will be conducted at the Queen Merry Hospital which is under the Hong Kong HA. Unlike many hospitals in the West and in China, acupuncture has become a routine in-patient service [45–47]. However, currently, acupuncture is not available in the Hong Kong HA system. The present study is designed to investigate whether it is feasible, effective and safe to use acupuncture as an adjunctive therapy for patients who suffer from postoperative pain and discomfort. If successful, the study would provide useful information for integrating acupuncture into perioperative care as part of the effort of integrating Chinese and Western medicine in Hong Kong hospitals.

This study protocol faces several challenges and limitations. Firstly, patients with different types of gynecological neoplasia requiring laparotomy will be included, which may create variability in the population. However, as wound pain is the main target of treatment, the variation of types of neoplasm would not be a great problem. To address this issue, only patients with midline incision are recruited, which would likely involve similar degrees of wound pain being experienced by each patient. In addition, randomization will be done rigorously so that the types of neoplasm in the two groups can be balanced.

Secondly, although in many of the previous trials on postoperative abdominal surgical pain, acupuncture was performed before the induction of anesthesia in the operating theater [3, 13, 31], it is infeasible to conduct preoperative acupuncture in our operating theaters which will lengthen the interval time between preoperative acupuncture being performed and the actual operation. This is because the surgical team was concerned about the underlying risks and potential liability. Therefore, in this trial, preoperative treatment will be carried out in the ward within 2 h before the operation.

Thirdly, the surgery time is uncertain and often varies due to the nature of the various underlying diseases, making it difficult to schedule an acupuncture treatment. To solve this problem, preoperative acupuncture will be arranged based on the estimated time of the operation list and the first postoperative treatment will be done upon arrival on the ward. The exact operation time and acupuncture treatment time will be recorded for further analysis.

Fourthly, it is not appropriate to regard sham acupuncture as a mere placebo or control group, although non-insertion sham acupuncture has been chosen in this study to maximize the treatment between the two groups [48]. Treatment costs incurred in the sham acupuncture arm involve sham acupuncture needles which will be assumed to cost the same as the acupuncture needles. The treatment efficacy of the sham acupuncture will not be assumed to be the same as that for the control group. In line with a previous randomized, sham-controlled trial alongside cost-effectiveness analysis of acupressure [49], the sham arm was one of the study arms for effectiveness and cost-effectiveness evaluation. Therefore, sham acupuncture will be considered as one competing intervention in the cost-effectiveness analysis.

Though there are many difficulties, the quality of the trial will be closely monitored by the Data and Safety Monitoring Board (DSMB) which is an independent board composed of a biostatistician, a senior Chinese medicine practitioner, and an anesthesiologist. It is hoped that this study will provide high-quality evidence on the efficacy and safety of acupuncture for alleviating postoperative pain as well as useful information for health economic analysis.

We hope that our findings will advance knowledge on the effectiveness of acupuncture in routine integrative medicine practice in Hong Kong hospital settings.

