### Health economic evaluation

The cost-effectiveness analysis will be performed using incremental cost-effectiveness ratio of acupuncture vs sham acupuncture, i.e., (cost of acupuncture minus cost of sham acupuncture)/(effectiveness of acupuncture minus effectiveness of sham acupuncture) as a health economic outcome.

The perspective of health service provider will be adopted when evaluating the costs of implementation of acupuncture as an adjunct treatment in the postoperative pain management in public inpatient setting. Only direct medical costs for two groups will be calculated. The costs to be included are staff time costs and treatment cost for patients. To estimate the staff time cost for making referrals, the time spent on each participant by each staff member will be recorded. The average number of minutes spent will be multiplied by the relevant salary rate per minute. The length of hospital stay will be recorded to estimate the cost by the multiplication of the number of inpatient days with inpatient hospital stay cost per day according to the most updated Government Gazette.

The acupuncture treatment cost will be estimated for each treatment in terms of acupuncturist’s time spent on delivering the treatment, including traveling time, multiplied by salary rate per minute. The cost of analgesics, acupuncture needles and other consumable will be calculated. The capital cost included the electric stimulator with 10% annual maintenance fee.

The effectiveness of acupuncture and sham acupuncture groups will be measured by quality-adjusted life expectancy using the AUC method which aggregates the PBMH value, measured by either SF-6D or EQ-5D-5 L, from baseline day to the study end day.

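### The planned acupuncture-versus-sham ICER subtracts out most of the cost of delivering acupuncture, so on its own it does not give the provider-perspective evaluation of implementation that the article sets out

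*Protocol article*

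**What the plan says.** The Health economic evaluation section of the protocol article defines the ratio as "cost of acupuncture minus cost of sham acupuncture)/(effectiveness of acupuncture minus effectiveness of sham acupuncture". It states the purpose and viewpoint in these words: "The perspective of health service provider will be adopted when evaluating the costs of implementation of acupuncture as an adjunct treatment". On scope it says "Only direct medical costs for two groups will be calculated". The delivery items are listed there: "The acupuncture treatment cost will be estimated for each treatment in terms of acupuncturist’s time spent on delivering the treatment, including traveling time", then needles and other consumables, then "The capital cost included the electric stimulator with 10% annual maintenance fee". Hospital stay, analgesics and staff time for referral are costed as well.

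The fourth limitation in the Discussion says that the sham arm's treatment costs include "sham acupuncture needles which will be assumed to cost the same as the acupuncture needles", and concludes that "sham acupuncture will be considered as one competing intervention in the cost-effectiveness analysis".

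The Procedure part of the Sham acupuncture group section gives sham the same time points, session length and number of sessions as real treatment. One practitioner treats both arms, and the sham needles are wired to a stimulator with no output. The Discussion also says that the hospital system concerned has no acupuncture service at present, and that the trial should inform its introduction.

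**The concern.** A provider with no acupuncture service chooses between usual care with acupuncture and usual care without it. Its main new expense is delivery: practitioner time and travel, needles and the stimulator. If the sham arm is charged nearly the same delivery cost, subtraction removes that expense from the ratio. What remains is a difference in bed days and analgesics between two arms of 36. A reader who takes the ratio as the cost-effectiveness of introducing acupuncture could then see a therapy that looks nearly free, or even cost-saving, because the sham arm was billed for a service that no provider would buy.

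**Working it through.** The article states no cost, QALY or ICER figure, so there is nothing to reproduce. The check is an algebraic split of the stated formula, followed by an illustration on assumed values.

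**Split of the numerator.** Let D be delivery cost per patient (acupuncturist time with travel, needles and consumables, stimulator with maintenance). Let R be the between-arm difference in hospital stay, analgesics and referral time. Then

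numerator = (D_acupuncture − D_sham) + R.

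| Delivery item | What the article fixes | Difference between arms |
|---|---|---|
| Needles | Equal price assumed (Discussion); same point-selection principle and schedule (Procedure) | 0, session for session |
| Acupuncturist time and travel | Same session length, number, time points and practitioner (Procedure); minutes to be measured (Health economic evaluation) | Probably close to 0 |
| Stimulator | Connected in both arms, inactive in sham (Procedure) | Probably close to 0 |

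So the numerator is approximately R.

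**What cancels, at most.** Seven sessions (Treatment protocol) of 30 minutes' stimulation (preoperative treatment section) give 7 × 30 = 210 min = 3.5 h. Body needles number 18 + 6 × 14 = 102. Auricular needles, travel and the stimulator come on top. These are maxima, because the article foresees discharge before day 5. The 30 minutes is stimulation time, not measured practitioner time.

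**If cancellation is only partial.** Write D_sham = f × D and take D = 1000 units (assumed). The delivery cost left in the numerator is 1000 × (1 − f):

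- f = 1: 0
- f = 0.9: 100
- f = 0.8: 200
- f = 0.5: 500

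**Effect on the ratio.** Assumed: D = 1000, a horizon of about 6 days from baseline to study end, and utility gains of 0.02, 0.05 and 0.10. QALY gain = utility gain × 6/365.25. The planned ratio (with f = 1) is R/QALY gain. The implementation ratio (sham delivery cost set to 0) is (1000 + R)/QALY gain.

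| Utility gain | QALY gain | Planned, R = 0 | Implementation, R = 0 | Planned, R = −200 | Implementation, R = −200 |
|---|---|---|---|---|---|
| 0.02 | 0.000329 | 0 | 3,043,750 | −608,750 | 2,435,000 |
| 0.05 | 0.000821 | 0 | 1,217,500 | −243,500 | 974,000 |
| 0.10 | 0.001643 | 0 | 608,750 | −121,750 | 487,000 |

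With R = −200 the planned numerator is −200 (acupuncture looks cheaper and better), while the implementation numerator is 1000 − 200 = +800. With R = −1000 the implementation numerator is 1000 − 1000 = 0. Only savings larger than the full delivery cost make both ratios cost-saving.

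**The case against.** The strongest reply is that the plan is consistent on its comparator. The fourth objective at the end of the Background, the Abstract and the formula all name sham. The Discussion discloses the choice, gives reasons and points to an earlier sham-controlled economic evaluation. This stands: a reader might infer that the ratio departs from its objective, and it does not. The tension is between the sham comparator and the stated aim of "evaluating the costs of implementation of acupuncture as an adjunct treatment in the postoperative pain management in public inpatient setting". Disclosing the choice does not resolve that.

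Second, only needle price is equated outright. Nothing says in terms how practitioner time or the stimulator is charged to sham. Time is to be measured, and real needles are manipulated while sham needles are only taped in place. This also stands. A reader might infer that the whole delivery cost cancels by construction. The article supports exact cancellation for needles only; for the rest it is an inference from costing both groups and from matched sessions.

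Third, it would be wrong to say that delivery cost is never counted. The article lists its components in detail. The cost is measured and then differenced out.

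Fourth, a ratio with zero sham delivery cost but sham-arm outcomes is a hybrid. Its effects, stay and analgesic use are not those of usual care. This is a fair reason not to let it replace the planned ratio. A reader might add that the hybrid is conservative against usual care, but that needs an effect of sham over usual care, which a two-arm trial cannot estimate.

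**Conclusion.** The concern holds in a limited form. The planned ratio answers how acupuncture compares with sham when both are billed as delivered. It contains little of the delivery cost that a provider would face, so it does not by itself support a conclusion about implementation. Cancellation is exact for needles and probably near-complete for time, travel and stimulator. If sham delivery cost 80 to 90% of real delivery, only 10 to 20% of that cost would stay in the numerator.

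The shift of roughly 0.6 to 3.0 million units per QALY for each 1000 units of cancelled cost, and the change of sign at R = −200, depend on assumed costs, horizon and utility gains. They show sensitivity to a very small QALY denominator and are not predictions. The point affects a secondary economic objective and leaves the primary pain analysis untouched.

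**What to change.** Keep the planned acupuncture-versus-sham ICER and state which delivery costs the sham arm bears in it. Beside it, prespecify an implementation ICER in which sham-session, sham-needle and sham-arm stimulator costs are zero and the acupuncture arm carries its full delivery cost. Report delivery cost per patient separately. Base any cost-effectiveness or implementation conclusion for the provider on that second analysis.

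State as a limitation that effects, hospital stay and analgesic use are still measured against sham, and that outcomes under usual care alone are not observed.

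The change uses resource data already due to be collected and does not touch randomization, treatment or assessments. It costs a small amount of extra analysis and yields a ratio less favourable to acupuncture.

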### Trial status

The first patient was recruited on 12 October 2016. Patient recruitment is being continued.

## Abbreviations

AA: Auricular acupuncture
ASA: American Society of Anesthesiologists
AUC: Area under the curve
CI: Confidence interval
Co-Is: Co-investigators
CONSORT: Consolidated Standards of Reporting Trials
DSMB: Data and Safety Monitoring Board
EA: Electroacupuncture
EQ-5D-5 L: EuroQol-5 Dimension-5 Level
HA: Hospital Authority
ITT: Intention-to-treat
*n*: Number of sample
NIH: National Institutes of Health
NMDAR: *N*-methyl-d-aspartate receptor
NRS: Pain Numerical Rating Scale
PBMH: Preference-based measure of health
PCA: Patient-controlled analgesia
PI: Principal investigator
QoR-9: Quality of Recovery- 9
SF-6D: Short Form-6 dimension
SPIRIT: Standard Protocol Items: Recommendations for Interventional Trials
SPSS: Statistical Product and Service Solutions
STRICTA: Standards for Reporting Interventions in Controlled Trials of Acupuncture
